### Trial status

Protocol version 1.0, dated April 2, 2025. The recruitment period began on April 4, 2025, and we expect recruitment to be completed by March 2027.

## Figures and Tables

**Figure 1 F1:**
[figure not shown]
Primary hypothesized pathways for MILAP to address IPV-related factors driving mental health outcomes

**Figure 2 F2:**
[figure not shown]
Study Timeline Note: W=Women, H=Husband, MIL=Mother-in-Law

**Figure 3 F3:**
[figure not shown]
Recruitment Flow Note: WOREC: Women’s Rehabilitation Center WHRDs: Women Human Rights Defenders FCHVs: Female Community Health Volunteers CBOs: Community-Based Organizations RAs: Research Assistants W: Women H: Husband MIL: Mother-in-law EUC: Enhanced Usual Carev MILAP: Multi-component family intervention to lower depression and address intimate partner violence

**Table 1 T1:** 

Session Number	MILAP Session Type	Session Time	Focus	Participants
**1**	**MIL-DIL Sessions**	2 hours	Awareness of negative effects of IPV Discuss cultural norms and expectations Establish allyship	Woman and her MIL
**2**		2 hours	Gender empowerment Facilitate increased freedom of movement	
**3**		1 hour	Brief behavioral activation #1: list and plan rewarding activities	
**4**		1 hour	Brief behavioral activation #2: review experience + reinforce	
**5**	**Behavioral Couples Therapy (BCT) Sessions**	1 hour	Align on challenges, establish safety and trust Learn specific strategies to cope with stress	Couples: Woman and her Husband
**6**		1 hour	Revisit effectiveness of coping skills Understand and address communication challenges between partners	
**7**		1 hour	Activity to encourage caring behavior between partners Build communication skills	
**8**		1 hour	Active listening skills Review strategies to improve communication Addressing ongoing challenges, if necessary	
**9**	**Triad (Summary) Session**	1 hour	Review all lessons and prepare for long-term change	Woman, her husband and MIL

**Table 2: T2:** List of Key Variables and Measurement Tools

Screening Tools	Baseline	Follow-up (I, 3, 6, 9, and 12 month)
1. Screening Tool (W) International Violence Against Women Sumy (IVAWS) Patient Health Questionnaire-9: first 2 questions and 9^th^ question. If the score of PHQ-9 first 2 questions >3, then administer all PHQ-9 I f PHQ-9 trigger Q 9 is “More than half the days” or “Nearly every days”, then Administer 3 questions of Nepal Emergency Suicide Screener (NESS) Severity of Alcohol Dependence Questionnaire (SADQ)	1. Demographic Questions (W, H, MIL)	
	2. SRQS 21-item: Spousal relationship quality score (21 items) (W, H, MIL)	1. SQRS 21-item: Spousal quality relationship scale (21 items) (W, H, MIL)
	3. MILRQS 7-item: Mother-in-Law Relationship Quality Score (7 items) (W, H, MIL)	2. MILRQS 7-item: Mother-inLaw Relationship Quality Scale (7 items) (W, H, MIL)
	4. WAS 5-item: Women’s Autonomy Scale (4 items) (W, H, MIL)	3. WAS 5-item: Women’s Autonomy Scale measuring Freedom of Movement (4 items) (W, H, MIL)
	5. WHOQOL-BREF 9-item (psychological well-being and social functioning) (W)	4. WHOQOL-BREF 9-item (psychological well-being and social functioning) (W)
2. Severity of Alcohol Dependence Questionnaire (SADQ) for Husband and MIL (H, MIL)	6. RSES 10-item: Rosenberg Self-Esteem Scale (10 items) (W)	5. RSES 10-item: Rosenberg Self-Esteem Scale (10 items) (W)
	7. FSS Fear Survey Schedule (focused on injury and sexual aggression fear) (W)	6. FSS: Fear Survey Schedule (focused on injury and sexual aggression fear) (W)
	8. ASI 16-rttm (Anxiety Sensitivity Index) (W)	7. ASI 16-item (Anxiety Sensitivity Index) (W)
	9. GAD-7: Generalized Anxiety Disorder-7 (W)	8. GAD-7: General ized Anxiety Disorder-7 (W)
	10. PHQ-9: Patient Health Questionnaire-9 & NEpal Suicide Screener (NESS) (W)	9. PHQ-9: Patient Health Questionnaire-9 & NESS (W)
	11. PCL-C 17-item: PTSD Checklist for DSM-4 (W)	10. PCL-C 17-item: PTSD Checklist for DSM-4 (W)
	12. BAD5–5F 9-ilem: Behavioral Actuation for Depression Scale - (9 items) (W)	11. BADS-SF 9-item: Behavioral Activation for Depression Scale - (9 items) (W)
	13. IFVCS 63-item: Indian Family Violence and Control Scale (63 items) (W)	12. IFVCS 63-item: Indian Family Violence and Control Scale (G3 items) (W)
	14. SRPS 8-item: Sexual relationship power scale (8 items) (W, H)	13. SRPS S-item. Sexual relationship power scale (8 items) (W, H)
	15. Adverse Childhood Experiences (W, H, MIL)	
	16. Additional 3 question from IVAWS on experiencing IPV to Mother-in-law (MIL)	
	17. GEMS 4-item: Gender Equality Men Scale (4 items) (W, H, MIL)	14. GEMS 4-item: Gender Equality Men Scale (4 items) (W, H, MIL)
	18. WHODAS 2.0 12-item: World Health Organization Disability Assessment Schedule 2.0 (12 items) (W)	15. WHOOAS 2.0 12-item: World Health Organization Disability Assessment Schedule 2.0 (12 items) (W)

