#### Exclusion criteria

Any participant with severe alcohol dependence defined by the Severity of Alcohol Dependence Questionnaire (SADQ) score ≥ 31.(69) Any participant with mild to moderate dependence will be referred but not excluded.History of IPV severe enough to result in hospitalization in the past 12 months, as MILAP is not designed to address severe levels of violence. Any participant reporting severe IPV cases requiring hospitalization will be referred to tertiary care facilities.Any participant with severe depression, defined by the Patient Health Questionnaire-9 (PHQ-9) score>19 and/or high suicide risk assessed by ninth question of the PHQ-9 (“thoughts that you would be better off dead or thoughts of hurting yourself in some way”) (70) and the Nepal Emergency Suicide Screener-3 (NESS-3) adapted from the Ask Suicide-Screening Questions(71), will be referred to specialized mental health centers for assessment. After discharge from the healthcare facility, they will be approached again for eligibility.Woman who is pregnant; since pregnancy changes the family dynamics and in our study settings, pregnant woman often temporarily moves back to live with their parents where the source of IPV is no longer around. However, if any participant becomes pregnant during the study, she will continue in the study.Cognitive problems/disability precluding participation as self-reported by participant.

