#### Participant timeline {13}

After the consent process is completed, we will conduct baseline assessments. This will be followed by the 1:1 random allocation of the recruited participants to either MILAP or EUC. Participants will then receive the intervention based on their allocation. We will conduct follow-up assessments at 1, 3 6, 9, and 12 months from baseline for all participants, regardless of intervention allocation. To evaluate the effectiveness of individual MILAP components, the one-month follow-up assessment will take place immediately after the completion of all MIL-DIL sessions and prior to the start of the BCT sessions. The three-month follow-up will be conducted after participants have completed all nine MILAP sessions. Figure 2 below shows the study timeline.

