### Safety monitoring & management

We will implement a standardized risk management system informed by findings from MILAP pilot studies, guidance from the community advisory board, and prior mental health research conducted by our team. During each intervention and assessment session, counselors and assessment staff will check in with participants regarding any recent incidents of IPV or other safety concerns. Any cases requiring urgent attention will be managed according to a pre-established crisis counseling and referral protocol.

During each assessment, assessment staff will administer PHQ-9, which includes a question on suicidality, to women participants. If a participant indicates any risk of suicidality, the assessment staff will administer the NESS-3. Patients identified as being at high and acute suicide risk will be immediately connected with a contracted crisis counselor for further evaluation and support. If immediate intervention is required, we will coordinate with the participant’s emergency contact and refer them to tertiary care facilities or OCMCs in their district. If no urgent referral is needed, the participant will be provided with a resource card containing contact information for relevant support services. In both scenarios, a study team member and the crisis counselor will follow up within 48 hours to ensure the participant’s safety and well-being. Severe IPV cases requiring medical attention will be referred to OCMCs at tertiary hospitals for mental health services, legal aid, medical care, shelters, and support from the community-based organizations. We will connect women in need of shelter support to WOREC for safe house services.

The study team will document all these incidents on standardized forms. The Principal Investigators (PIs) will review these reports and adjust safety protocols as needed. The data and safety monitoring board will conduct semi-annual evaluations to ensure the safety of participants throughout the study.

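### The screening rule in Table 2 cannot by itself enforce the PHQ-9 >19 exclusion, and no stated step checks the full baseline PHQ-9 against that exclusion before allocation

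*Protocol article*

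**What the plan says.** **The exclusion.** The section Exclusion criteria {10} removes, and refers for specialist assessment, any participant with "severe depression, defined by the Patient Health Questionnaire-9 (PHQ-9) score>19 and/or high suicide risk assessed by ninth question of the PHQ-9" together with the three-question Nepal suicide screener (NESS-3). She may be approached again after discharge.

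**The screening form.** The first column of Table 2 asks each woman the "Patient Health Questionnaire-9: first 2 questions and 9^th^ question". The remaining items depend on a gate: "If the score of PHQ-9 first 2 questions >3, then administer all PHQ-9". The suicide screener has its own gate, which opens if "PHQ-9 trigger Q 9 is “More than half the days” or “Nearly every days”, then Administer 3 questions".

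**The sequence.** Under Who will take informed consent {26a}, research assistants settle a woman's eligibility at screening, before her husband and mother-in-law are screened. Participant timeline {13} then reads: "After the consent process is completed, we will conduct baseline assessments. This will be followed by the 1:1 random allocation of the recruited participants". The baseline column of Table 2 lists the PHQ-9 and NESS for all women with no gate.

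**Action at assessments.** Safety monitoring & management has the PHQ-9 given to women at each assessment and adds: "If a participant indicates any risk of suicidality, the assessment staff will administer the NESS-3". Women at high and acute suicide risk go to a crisis counselor. The section names no action for a PHQ-9 total above 19.

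**The concern.** The exclusion is defined on the nine-item total, but the form used to decide eligibility obtains that total only for women who score high on the first two items. A woman can carry her score mainly on the other seven items. She then passes screening although the protocol says she should be excluded and referred.

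The baseline PHQ-9 comes in time to catch her, but the text gives it no role in eligibility. Under Concealment mechanism {16b}, baseline is done by assessment staff whose sole task is assessment, whereas the research assistants do the screening. Without a stated hand-back, the score can be recorded and allocation can go ahead.

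The stake is participant safety and eligibility, not bias. Any such woman enters before allocation, so the arms stay comparable in expectation. But she would be randomised in breach of the protocol's own safety criterion, in a trial whose first primary outcome is built on the same scale.

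**Working it through.** The plan gives no figure to reproduce here. The check is whether a total above 19 is possible below the gate.

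**Inputs**
- Exclusion: total >19 (Exclusion criteria).
- Gate to the full scale at screening: items 1+2 >3 (Table 2).
- Screener trigger at screening: item 9 in its two highest categories (Table 2).
- Assumption: each item is scored 0, 1, 2 or 3, so the two highest categories score 2 and 3. The article does not state the scoring.

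**Step 1. Highest total below the gate.** Let k be the sum of items 1 and 2. The other seven items add at most 7 × 3 = 21, so the maximum is k + 21. To exceed 19, those seven items must sum to at least 20 − k.

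| k | Maximum total | Needed from the other seven items (of 21) |
|---|---|---|
| 0 | 21 | 20 |
| 1 | 22 | 19 |
| 2 | 23 | 18 |
| 3 | 24 | 17 |

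Every maximum exceeds 19, so the gate cannot guarantee the exclusion. The last column shows how narrow the route is.

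**Step 2. Does item 9 close the gap?** Not fully. With k = 3 and item 9 at 1, the maximum is 3 + 1 + 6 × 3 = 22. With item 9 at 0 it is 3 + 0 + 18 = 21. A woman with the latter pattern gets neither the full scale nor the suicide screener at screening.

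**Step 3. Response patterns.** Of the 4⁹ = 262,144 possible patterns, 9,460 total more than 19. For those below the gate, the seven items may fall short of 21 by at most k + 1. The number of seven-item patterns meeting this is 8, 36, 120 and 323 for k = 0, 1, 2, 3, and the number of pairs for items 1 and 2 is 1, 2, 3 and 4:

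1×8 + 2×36 + 3×120 + 4×323 = 8 + 72 + 360 + 1,292 = 1,732.

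So 1,732 of 9,460 patterns (18.3%) never reach the full PHQ-9 at screening, and 166 (1.8%) also miss the item 9 trigger. These count patterns and are not prevalences. Items correlate, so the share among real women would be lower.

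**Step 4. If the gate were meant as ≥3.** Only k = 0, 1, 2 would then be missed: 8 + 72 + 360 = 440 patterns (4.7%), with a maximum of 23. The gap shrinks but stays open.

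**Step 5. What happens next, as written.** Take items 1+2 = 3, item 9 = 0 and the other six items at 3, total 21.
- Screening: gate not opened, exclusion not assessed.
- Baseline: if she answers the same way, a total of 21 is recorded and her item 9 answer triggers nothing.
- Next stated step: allocation.

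**Secondary: the suicide-screener trigger.** An item 9 answer in the lowest non-zero category does not open NESS at screening under Table 2. Read naturally, it does lead to NESS-3 under the any-risk wording of Safety monitoring & management. The crisis counseling text under Intervention description {11a} uses item 9 and NESS-3 without stating which answers trigger the latter.

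**The case against.** The strongest reply is that nobody is missed in practice. Item 9 is put to every woman at screening whatever she answers on items 1 and 2. The ungated PHQ-9 and NESS are in the baseline battery, which the Abstract and the timeline both place before randomisation, and the wider safety trigger applies there. This stands, and it rules out a reading that a reader might be tempted to make: that severely depressed or suicidal women can be randomised with nothing on record. Their totals and item 9 answers are recorded before allocation, and high suicide risk at baseline leads to crisis counseling.

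It does not close the point. Recording a score is not the same as applying a criterion to it, and the safety text acts on suicidality and violence, not on the total.

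A second reply is that the exclusion covers any participant with severe depression and so extends implicitly to baseline, that Table 2 is a list of instruments, and that the full protocol or the recruitment and timeline figures, which are not shown, may contain a recheck. That may be so. But the gate is printed as a rule, and as printed it does not deliver the exclusion.

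Third, the two screener triggers belong to different stages, and a narrower trigger may suit an exclusion aimed at high risk. This largely stands and makes that point secondary. It still needs reconciling, because NESS-3 is part of the exclusion and the narrower trigger sits where eligibility is decided.

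Finally, the table text is visibly garbled in places, so >3 might be a misreading of ≥3. Step 4 shows that the conclusion does not depend on it.

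**Conclusion.** The point holds in limited form. The screening rule in Table 2 cannot by itself enforce the PHQ-9 >19 exclusion, since totals of 20 to 24 are possible below the gate. The visible text does not tie the baseline score to eligibility. A woman whom the protocol excludes can therefore be randomised without the exclusion being applied.

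This rests on 0–3 item scoring and on the article text alone. The route is narrow: at least 17 of 21 points on the other seven items, with 3 or less on the first two. A reader might take 18.3% as a miss rate or want a number of women out of 300. The document supports neither, because it gives no distribution of item responses. The correction is still worth making: it concerns a safety exclusion, and Trial status expects recruitment to run to March 2027.

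**What to change.** Reconcile Exclusion criteria, Who will take informed consent {26a}, Participant timeline {13} and Table 2, so that the protocol's existing PHQ-9 exclusion is checked on the full baseline PHQ-9 for every woman before allocation. State who makes the check and who tells the data manager. No threshold needs to change.

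Separately, reconcile the NESS trigger across Table 2, Exclusion criteria, the crisis counseling text and Safety monitoring & management. Which trigger applies at each stage is for the clinical team.

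The cost is form and protocol wording, with no new instrument or visit. A few women may be found ineligible after completing baseline and would have to be replaced. Because this happens before randomisation, it does not affect the intention-to-treat comparison or the blinding of assessors.

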## Data Availability

The de-identified participant-level data will be shared with the National Institute of Mental Health (NIMH) Data Archive. We will publicly share all statistical codes when sharing findings of this study.

## Abbreviations

AE: Adverse Event
BCT: Behavioral Couples Therapy
CBT: Cognitive Behavioral Therapy
DIL: Daughter-in-Law
DM: Data Manager
EUC: Enhanced Usual Care
FOM: Freedom of Movement
HIPAA: Health Insurance Portability and Accountability Act
IDI: In-depth Interview
IFVCS: Indian Family Violence and Control Scale
IPV: Intimate Partner Violence
ITT: Intention-to-Treat
IVAWS: International Violence Against Women Survey
LMIC: Low and Middle-Income Country
MIL: Mother-in-Law
MILAP: **M**ulti component family **I**ntervention to **L**ower depression and **A**ddress intimate **P**artner violence
NESS: Nepal Emergency Suicide Screener
NIMH: National Institute of Mental Health
OCMC: One stop Crisis Management Center
PCL-C: Post-traumatic Stress Disorder (PTSD) CheckList-Civilian Version
PHQ-9: Patient Health Questionnaire-9
PI: Principal Investigator
PTSD: Post-traumatic Stress Disorder
RCT: Randomized Controlled Trial
REDCap: Research Electronic Data Capture
SADQ: Severity of Alcohol Dependence Questionnaire
SCT: Social Cognitive Theory
SD: Standard Deviation
WOREC: Women Rehabilitation Center
